### Statistical Analysis Plan

#### Primary Analysis

Paired *t* tests will be used to detect the improvement in depression score (ie, PHQ-8) and anxiety score (ie, GAD-7) from baseline to follow-up measured 60 days later. Two-sample *t* tests will be used to examine the difference in improvements between the UR and RL groups. The mood ratings of each participant will be collected each day over the 60-day study period. We will also compare the average of daily mood rating improvements compared to baseline (ie, each consecutive daily measure minus the baseline measure) between these two groups using a longitudinal data analysis approach (eg, generalized estimating equation [GEE]). We will not compare the baseline characteristics between the samples in each arm. This practice could potentially be misleading because any differences would be due to chance [26-28].

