## Methods

### Design

This study has various designs: (1) a pre-post comparison, in which we assess changes in depression and anxiety for all patients before and after the intervention; (2) a randomized controlled trial with two groups, RL and UR; and (3) an MRT, only within the UR group.

Randomization will be performed as block randomization with a 1:1 allocation. Participants will be automatically randomized into groups through our secure server during onboarding of the study, ensuring allocation concealment. Participants will be informed of the nature and frequency of the messages they will be receiving. They will be blinded to their group randomization. Further, if messages are not sent out appropriately, research assistants will contact the developer to address errors (eg, when individuals do not receive messages, or they receive messages out of the specific time bounds). Throughout the study, the researchers will check whether the randomization of messages is functioning adequately approximately once every two months. The necessity of these steps makes it infeasible to blind the researchers. Microrandomization will happen automatically on a daily basis through our secure server. We used the SPIRIT (Standard Protocol Items: Recommendations for Interventional Trials) checklist when writing this protocol [17]. Figure 1 shows our study design.

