### Measures

For our primary outcomes, we will administer a survey at baseline and at 60-day follow-up, which includes the PHQ-8 [19] and GAD-7 [20]. In addition to these questionnaires, we will also ask open-ended questions to assess how participants are impacted by COVID-19. Questionnaire data will be stored on UC Berkeley’s Qualtrics platform. Our secondary outcome, daily mood ratings, will be collected via text message on a daily basis and stored on the HealthySMS platform. The project coordinator and research assistants will be responsible for managing patient data collection. Once data from all participants are collected, they will be stored on UC Berkeley’s Secure Box, a secure cloud-hosted platform. See Table 1 [21,22] for all included questionnaires and timing of their administration.

**Table 1 table1:** Questionnaires included in the StayWell at Home study and timing of administration.

Questionnaire^a^	Baseline	Follow-up
PHQ-8 (8-item Patient Health Questionnaire)^b^	X^c^	X
GAD-7 (7-item Generalized Anxiety Disorder) scale^b^	X	X
COVID-19 questions	X	X
System Usability Scale^d^	N/A^e^	X

^a^The measures were taken from validated questionnaires in English and Spanish.

^b^The PHQ-8 depression scale and the GAD-7 anxiety scale were not modified.

^c^X indicates that the measure was administered at this time point.

^d^The System Usability Scale [21] was modified to decrease literacy levels, using the Flesch-Kincaid readability test [22].

^e^N/A: not applicable; the measure was not administered at this time point.

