#### Secondary Analysis

For the UR intervention group, the differences in proximal outcome (ie, daily mood rating assessed 3 hours after the message sent) between both message categories (ie, BA versus coping skills) or among the time windows (ie, reference level versus the other three levels) will be examined using the weighted and centered least-squares (WCLS) method for longitudinal data analysis under the multilevel MRT design proposed by Xu et al [24]. This method is similar to the GEE approach. The independent working correlation matrix will be adopted. The covariates include days in study (ie, from 1 to 60 days), day of the week (ie, Monday-Sunday), intervention component (ie, message or time window), and the interaction term between days and intervention component. The trend of the intervention effect over days can be constant, linear, or quadratic. The message or the time window component categories will be converted to dummy variables, and each of these will be centered by the corresponding randomization probabilities (ie, 0.5 and 0.33 for each level of the message and time components, respectively).

The mood rating changes from baseline will be categorized into binary outcomes (ie, high [greater or equal to the median of the whole sample] or low [less than the median]). The WCLS estimator under the MRT design for binary outcome proposed by Qian et al [29] can be applied to the message component (ie, two-level intervention). For the timing (ie, three-level) component, we will propose the novel WCLS method by combining the ideas of both Xu et al [24] and Qian et al [29]. This method can also be extended to model the mood ratings as ordinal outcome variables. 

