### Power Analysis

We will perform sample size calculation at the usual 80% power at 5% level of significance.

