#### Primary Analysis

The Cohen methods [30] were used to calculate sample sizes for primary hypotheses. At a medium standardized effect size (ie, Cohen *d*=0.5), a total sample size of 64 is required to detect an improvement of either the depression or anxiety score from baseline to 60-day follow-up, and a sample size of 128 to detect differences between the UR and RL groups.

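### The RL-versus-UR t test on change in PHQ-8 and GAD-7 is valid, but adjusting for the baseline score already collected would be more precise at no cost in data

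*Protocol article*

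**What the plan says.** Under Measures, the article states "we will administer a survey at baseline and at 60-day follow-up, which includes the PHQ-8"; the GAD-7 is given in the same survey. Each participant who completes follow-up therefore has a baseline and a day-60 value on both scales.

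Under Statistical Analysis Plan, Primary Analysis, the change within all participants is tested with paired t tests. For the randomized comparison, two-sample t "tests will be used to examine the difference in improvements between the UR and RL groups". No baseline covariate is named, and the Sensitivity Analysis list has no baseline-adjusted analysis of these two scales.

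The Power Analysis works at "80% power at 5% level of significance". "At a medium standardized effect size" (Cohen d=0.5), it requires "a sample size of 128 to detect differences between the UR and RL groups". Allocation is by "block randomization with a 1:1 allocation". The closing paragraph of the Power Analysis describes the UR-RL difference in depression and anxiety as the primary aim.

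**The concern.** A change score does use the baseline, but it assumes that each point of baseline difference carries over as one full point at day 60. When the correlation between the two visits is below 1 and their variances are similar, the true slope is below 1. Subtracting the whole baseline then adds noise. ANCOVA estimates the slope and removes that noise, using only variables the trial already collects.

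What is at stake is the width of the confidence interval, and the power, for the RL-UR difference on both scales. The two arms draw on the same message bank and differ only in how messages are selected and timed, so the true difference may well be smaller than d=0.5. Precision is worth having in that case.

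**Working it through.** **Inputs from the article.** 80% power, 5% level, d=0.5, 128 in total, 1:1 allocation; 15% dropout (used in the secondary sample-size calculations only); 229 enrolled as of August 24, 2020 (Results).

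**Assumptions.** The test is two-sided (not stated, but it reproduces 128). The baseline to follow-up correlation r of PHQ-8 and GAD-7 is not given, so a range of 0.3 to 0.8 is used. The correlations of 0.2 and 0.4 in the Power Analysis concern daily mood improvements and do not apply here. The article does not say which SD d refers to; the main calculation takes the SD of the change score.

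**Step 1: the plan's own figure.** A two-sample t test with d=0.5, two-sided 5% and 80% power needs 63.77 per arm, hence 64 per arm and 128 in total. Power at 64 per arm is 80.1%. The stated 128 is reproduced.

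**Step 2: variance ratio.** Let s0 and s1 be the SDs at baseline and day 60.

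- Change score: s0² + s1² − 2·r·s0·s1
- ANCOVA: s1²(1 − r²)
- Difference: (s0 − r·s1)², which is never negative

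Apart from the one degree of freedom spent on the slope, ANCOVA is therefore no less precise. With s0 = s1 = s the ratio is s²(1 − r²) / [2s²(1 − r)] = (1 + r)/2. A simulation with 64 per arm gave ratios of 0.651, 0.757 and 0.860 at r = 0.3, 0.5 and 0.7, against 0.65, 0.75 and 0.85 from the formula.

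**Step 3: size with equal variances.** The effective d for ANCOVA is 0.5/√((1+r)/2). For the 229 enrolled, 229 × 0.85 ≈ 195 analysed, or about 97 per arm.

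| r | Variance reduction | SE reduction | Total N for 80% power | Power, 128 analysed | Power, about 195 analysed |
|---|---|---|---|---|---|
| Planned t test | – | – | 128 | 80.1% | 93.5% |
| 0.3 | 35% | 19% | 84 | 93.6% | 99.1% |
| 0.5 | 25% | 13% | 98 | 90.0% | 98.0% |
| 0.7 | 15% | 8% | 110 | 86.1% | 96.4% |
| 0.8 | 10% | 5% | 116 | 84.1% | 95.5% |

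**Step 4: unequal variances.** Take s0 = 1 and s1 = 1.2.

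- r = 0.5: change 1 + 1.44 − 1.2 = 1.24; ANCOVA 1.44 × 0.75 = 1.08; reduction 1 − 1.08/1.24 = 13%
- r = 0.7: change 1 + 1.44 − 1.68 = 0.76; ANCOVA 1.44 × 0.51 = 0.7344; reduction 1 − 0.7344/0.76 = 3%

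If day-60 scores vary less than baseline scores, the reduction exceeds that in the table.

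**Step 5: if d=0.5 refers to the raw-score SD.** With equal variances and 128 analysed, the change-score test has 66%, 80% and 95% power at r = 0.3, 0.5 and 0.7. ANCOVA has 84%, 90% and 98%.

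**The case against.** The strongest reply is that nothing here is wrong. Under randomization the change-score t test is unbiased and keeps its type I error, and the sample size matches the test. That stands in full.

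The second reply concerns size. The article gives neither r nor any SD, so a reader might infer that a large share of the precision is lost, but the document does not establish this. The reduction is about 10% if r is 0.8, and only 3% at r = 0.7 if the follow-up SD is 1.2 times the baseline SD.

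Third, one could apply 15% dropout to exactly 128 (about 54 per arm) and start from 73% power. That is not this trial's position. The Power Analysis treats 128 as a minimum, and 229 were already enrolled. Any shortfall from leaving dropout out of the 128 is a separate sample-size matter, not a cost of the t test.

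Two further readings are tempting and do not hold:

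- **Chance baseline imbalance as a second harm.** The over-correction of a chance imbalance by the change score averages to zero over randomizations. It is the same efficiency loss seen from another side.
- **The microrandomized analysis.** Its covariate list begins "The covariates include days in study (ie, from 1 to 60 days), day of the week (ie, Monday-Sunday" and names no earlier mood rating or baseline severity. But a list introduced in that way need not be complete, and the full analysis plan may hold further control variables. Any figure for the loss would also rest on assumed within-person correlations. This analysis is secondary, and the point does not extend to it.

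**Conclusion.** This is a free improvement and not an error. The planned RL-UR test is valid and 128 is right for it, but ANCOVA answers the same question with a smaller variance: 10% to 35% smaller for r between 0.8 and 0.3, assuming equal variances at the two visits. The direction does not depend on that assumption; the amount does, and it also depends on a correlation that the article does not report.

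At d=0.5 on the change SD, the power gain is 4 to 14 percentage points at 128 analysed and about 2 to 6 points at the current enrolment after 15% dropout. In the second case power is already ample for d=0.5. The practical benefit is a narrower interval, which matters most if the true RL-UR difference is smaller than the one assumed.

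**What to change.** In Statistical Analysis Plan, Primary Analysis, make the primary RL-UR comparison a linear model of the day-60 PHQ-8 score on arm and baseline PHQ-8, with robust standard errors. Report the adjusted mean difference with its confidence interval. Do the same for GAD-7 with its own baseline value. Move the two-sample t test on change to the sensitivity analyses. The paired pre-post tests are unaffected, and the 128 can stay as a conservative minimum for the number analysed.

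The cost is a change of wording. Both scores are already collected, and one degree of freedom is spent. The change should be made and dated before outcomes are compared by arm.

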#### Secondary Analysis

For the UR intervention group, the differences in proximal outcome (ie, daily mood rating assessed 3 hours after the message sent) between both message categories (ie, BA versus coping skills) or among the time windows (ie, reference level versus the other three levels) will be examined using the weighted and centered least-squares (WCLS) method for longitudinal data analysis under the multilevel MRT design proposed by Xu et al [24]. This method is similar to the GEE approach. The independent working correlation matrix will be adopted. The covariates include days in study (ie, from 1 to 60 days), day of the week (ie, Monday-Sunday), intervention component (ie, message or time window), and the interaction term between days and intervention component. The trend of the intervention effect over days can be constant, linear, or quadratic. The message or the time window component categories will be converted to dummy variables, and each of these will be centered by the corresponding randomization probabilities (ie, 0.5 and 0.33 for each level of the message and time components, respectively).

The mood rating changes from baseline will be categorized into binary outcomes (ie, high [greater or equal to the median of the whole sample] or low [less than the median]). The WCLS estimator under the MRT design for binary outcome proposed by Qian et al [29] can be applied to the message component (ie, two-level intervention). For the timing (ie, three-level) component, we will propose the novel WCLS method by combining the ideas of both Xu et al [24] and Qian et al [29]. This method can also be extended to model the mood ratings as ordinal outcome variables. 

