### Secondary Analysis

We hypothesize that we will find differential effects on mood ratings for the two categories of messages and different timings (ie, microrandomized design).

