##### Uniform Random Policy

This study design is an MRT [16], where every day during the study treatment, allocation is characterized by a full factorial design with a total of two factors representing supportive *messages* and the *time frame* when the message was sent. The *messages* factor has two levels, and the *time frame* factor has three levels (ie, 9 AM-12 PM, 12 PM-3 PM, and 3 PM-6 PM). Each participant will be rerandomized to a new combination of *messages* and *time frame* every day. The study is set up so that each day participants will be randomized to receive one message out of the message categories (ie, BA vs other skills), constituting a multilevel MRT design with probabilities of 0.5 for the message categories and 0.33 for the timing. Thus, every participant will receive one BA or skill message per day and one mood check-in message.

This design allows us to understand the type and timings of text messages that most improve participants’ mood, which is a secondary aim of this study. MRTs enable the testing of specific intervention components, while still allowing for the evaluation of a causal, average treatment effect of the intervention [16]. Figure 2 shows our MRT design.

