#### Sensitivity Analysis

The following sensitivity analyses will be or can be performed:

Both the primary and secondary analyses will be repeated based on the participants with at least 45 out of 60 (75%) days of data.The change of the secondary outcome will be imputed using the last-observation-carried-forward method if either the corresponding pretest or posttest value is missing.We will conduct the secondary analyses—the effects of message categories and timings—in the RL group.An interaction between the components of the message and time window can be considered in the GEE model for the secondary hypothesis. This interaction term allows us to examine what type of message, sent at what time of the day, leads to the highest increase in daily mood ratings.

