#### Secondary Analyses

Using the GEE-based sample size calculation method [31,32] with a small standardized effect size (ie, Cohen *d*=0.2), with the correlation coefficients of 0.2 and 0.4 among the daily mood rating improvements compared to baseline, sample sizes of 84 and 161 are required to detect a group effect for either the UR or RL group, respectively, randomly allocated at baseline. Assuming 15% of the participants will drop out before the end of the study, a sample size of 190 is required for each group.

At a small standardized effect size (ie, Cohen *d*=0.1), with a constant trend of intervention effect over days, sample sizes of 55 and 76 are required to detect the average daily causal effects of message and time window, respectively, for the UR intervention group, using the WCLS-based sample size calculation method proposed by Xu et al under the multilevel MRT design [33]. Assuming each participant has an expected 70% response rate to the sent messages and 15% of the participants are expected drop off before the end of the study, a sample size of 126 is recommended for the UR group. 

Since our primary aim is to detect differences between the UR and RL groups for depression and anxiety scores, we aimed to include at least 128 participants. However, since our goal is also to provide a service during this unprecedented COVID-19 pandemic, we will continue to make the program available and recruit participants until at least April 2021 or for as long as funding allows.

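### The timing comparison is written as an unnamed reference against three other windows when only two others exist, and it is not the joint 2-df test that the stated size of 76 supports

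*Protocol article*

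**What the plan says.** All references are to the protocol article.

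- **Hypothesis** (Introduction, Secondary Analysis): the authors expect that "we will find differential effects on mood ratings for the two categories of messages and different timings".
- **Design** (Uniform Random Policy): each day a participant is randomised to one of two message categories (probability 0.5 each) and one of three time windows (0.33 each). On purpose, the section says: "This design allows us to understand the type and timings of text messages that most improve participants’ mood".
- **Analysis** (Statistical Analysis Plan, Secondary Analysis): differences between message categories, or "among the time windows (ie, reference level versus the other three levels) will be examined using the weighted and centered least-squares (WCLS) method". Component levels enter as dummy variables centred by their randomisation probabilities. No reference window is named, and no joint test of the windows is mentioned.
- **Sizing** (Power Analysis): "We will perform sample size calculation at the usual 80% power at 5% level of significance". On the micro-randomised part, the article states that "sample sizes of 55 and 76 are required to detect the average daily causal effects of message and time window, respectively". Both figures take d = 0.1 and assume that the effect does not change from day to day. The UR group is then raised to 126 for non-response and dropout. Degrees of freedom are not given.
- **Further analyses**: the same Secondary Analysis section adds a dichotomised outcome and a possible ordinal extension. The Sensitivity Analysis section adds a repeat in the reinforcement learning (RL) arm and an optional message-by-window interaction, meant to show "what type of message, sent at what time of the day, leads to the highest increase in daily mood ratings".

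**The concern.** The sentence that defines the timing comparison cannot be carried out as written, because a three-level factor has two non-reference levels. Once the count is corrected, two things remain unsettled.

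1. **Which test decides.** The sentence describes contrasts against a reference. The sample size appears to come from a different test, one that asks whether the three windows differ at all. If the contrasts decide, the stated power is not theirs, and two chances at 5% exceed 5% for the timing claim.
2. **Which question is answered.** The stated aim is to learn which timing most improves mood. Contrasts against one window do not display the comparison between the other two, and what they show depends on the window chosen as reference. Suppose one window differs from two equal ones. If the odd window is the reference, both contrasts carry the effect. If it is not, only one does.

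The Discussion intends these results to help optimise the intervention and to serve as preliminary evidence for a just-in-time adaptive version, so a window named as best should be distinguishable from chance.

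**Working it through.** **Inputs from the article.** 5% significance and 80% power; d = 0.1, constant over days; T = 60 days with one randomisation per day; probabilities 0.5 (message) and 0.33 (window); 70% response and 15% dropout ("Assuming each participant has an expected 70% response rate to the sent messages and 15% of the participants are expected drop off").

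**Assumptions.** Two-sided 5%; 0.33 taken as 1/3; noncentral-F Wald test.

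**Formula.** Power = P{F(p, N−p−q; λ) > F₀.₉₅(p, N−p−q)}, with λ = N·T·δ′Sδ. Here p is the number of effect parameters and S is the covariance matrix of the centred dummies. Taking q from 0 to 3 gives the same sizes.

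**Step 1: reproduce the plan's figures.**
- Message, p = 1: S = 0.5 × 0.5 = 0.25, so λ/N = 60 × 0.01 × 0.25 = 0.15. This gives **N = 55**, as stated.
- Timing, joint, p = 2: S has 2/9 on the diagonal and −1/9 off it. For δ = (0.1, 0.1) or (0.1, 0), δ′Sδ = 0.01 × 2/9, so λ/N = 60 × 0.01 × 2/9 = 0.1333. Power is 79.8% at 75 and 80.4% at 76. This gives **N = 76**, as stated.
- UR group: 70% response leaves 0.7 × 60 = 42 effective days, so λ/N = 0.0933 and N = 107. Then 107/0.85 = 125.9, which rounds up to **126**, as stated.

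**Step 2: size the comparison as written.** For one window against a reference, the inverse of S has diagonal 6, so λ/N = 60 × 0.01/6 = 0.10.

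| Timing test | N before inflation | N after 70% response and 15% dropout |
|---|---|---|
| Joint 2-df, 5% | 76 | 126 |
| One contrast, 5% | 81 | 115/0.85 = 135.3, so 136 |
| One window against the other two pooled, 2.5% | 74 | 124 |

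Of the timing tests tried, only the joint test gives both 76 and 126. At N = 76 a single contrast has about 78% power.

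**Step 3: error rate for timing when no window differs.** Two contrasts sharing a reference are correlated 3/6 = 0.5 (off-diagonal over diagonal of the inverse of S). Simulation with large-sample normal statistics and critical value 1.96:
- either of two reference contrasts: 9.0%
- any of the three pairs: 12.2%
- joint 2-df test: 5.0%

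**Step 4: pairwise contrasts after the joint test.** With three windows, any two of the pairwise equalities together imply that all three are equal. Testing the joint hypothesis at 5% and then each pair at 5% is therefore a closed procedure. If all windows are equal, the joint test holds the error at 5%. If exactly one differs, only one true equality remains, and it is tested at 5%. Simulation gave 5.0% in the first case and 4.7% in an example of the second.

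**The case against.** The strongest reply is that a joint test may already be intended. The text speaks of differences among windows, and dummy coding is how a three-level factor enters a joint Wald test. The exact match of 76 to 2 df points the same way. That stands: nothing in the article says timing will be judged by separate p values. But the only comparison it spells out is reference against others, with a wrong count, and it never names the joint test.

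The reply is also right that the power loss is small, 80% to about 78%. The article separately asks for 190 per group for the daily mood comparison. If the UR arm reached that, power for a single contrast would not be the issue. A larger sample does not cure the error rate.

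A reader might infer more, and the article does not support it:

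- **That every analysis is tested at full 5%, giving a much larger combined error rate.** The 5% is stated for sample size only. The interaction is an optional sensitivity analysis, and the binary method for messages and the ordinal extension are worded as possibilities. Dichotomising is planned, but nothing says a binary result alone would establish the hypothesis.
- **That message and timing must share 5%, for example by Holm.** Two independent tests at 5% give 1 − 0.95² = 9.75%, but these are distinct factors within a secondary aim. Judged at 2.5%, message at 55 and joint timing at 76 each fall to about 71% power. Restoring 80% for timing would need 127/0.85 = 149.4, so 150 UR participants. That is a trade-off for the authors, not an error.
- **That the best window cannot be identified.** The two non-reference windows can be compared from the same fit, as a difference of two coefficients with their covariance. The article simply does not plan to report it.

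**Conclusion.** The point holds in a limited form. The level count is wrong on the face of the text. The timing comparison described is not the test that yields 76 and 126. If the reference contrasts decided the timing claim, its false-positive rate would be about 9% (12% with all three pairs), and each contrast would have about 78% power at 76 and need 81, or 136 after inflation.

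That 76 is a joint 2-df size is inferred from exact reproduction of 55, 76 and 126, since the article does not give degrees of freedom. The error rates assume that either contrast at an unadjusted 5% would be claimed as a timing effect. The finding concerns what the printed analysis section says. It does not rest on the absence of a fuller multiplicity plan, which a separate analysis plan may contain.

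**What to change.** In the Secondary Analysis part of the Statistical Analysis Plan:

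1. Correct the count of non-reference windows from three to two, and name the reference used for coding.
2. State that the timing effect is judged by one joint 2-df WCLS Wald/F test of the three windows at 5%. This is the test that gives 76, and its result does not depend on the reference.
3. Report all three pairwise window contrasts with intervals, and call one window better than another only if the joint test rejects and that pair is significant at 5%.
4. State that the binary, ordinal, RL-arm and message-by-window interaction analyses are supportive, so that a best combination out of 2 × 3 = 6 is not claimed from them alone.

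**Cost:** wording only. Data, model and the sizes 55, 76 and 126 stay as they are. The one restriction is that a pairwise timing difference can no longer be claimed when the joint test does not reject.

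### The message and timing model in the uniform random arm leaves out the participant's earlier mood ratings: valid and powered as planned, but precision is forgone

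*Protocol article*

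**What the plan says.** The Secondary Analysis section of the Statistical Analysis Plan takes as outcome the mood rating given 3 hours after each day's message and analyses it by WCLS in the UR arm. On covariates it states: "The covariates include days in study (ie, from 1 to 60 days), day of the week (ie, Monday-Sunday), intervention component (ie, message or time window"), followed by the interaction of days with the component. It adds: "The independent working correlation matrix will be adopted". The treatment dummies are centred at the known probabilities, 0.5 for message category and 0.33 for time window. No earlier, lagged or baseline mood term is named.

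The Power Analysis section (Secondary Analyses) sizes this model: "sample sizes of 55 and 76 are required to detect the average daily causal effects of message and time window, respectively". The assumption behind both figures is given as "At a small standardized effect size (ie, Cohen *d*=0.1), with a constant trend of intervention effect over days". After allowing for response and dropout it recommends 126 for the UR arm. The same section sizes the comparison of UR with the reinforcement learning (RL) arm "with the correlation coefficients of 0.2 and 0.4 among the daily mood rating improvements compared to baseline", and arrives at 190 per group.

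Earlier ratings will be available: "The mood ratings of each participant will be collected each day over the 60-day study period". The Reinforcement Learning Policy section already uses past mood as learning data.

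**The concern.** Message category and time window are re-randomised every day within each person. A participant's usual mood level therefore carries no information about these contrasts and is noise for them. Study day and weekday do not absorb it, and neither does working independence, so the full between-person variance enters the standard errors. The article's own correlations for mood improvements suggest that this stable component may be substantial.

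Ratings from days before the current randomisation are pre-treatment for that day. Because the treatment dummies are centred at fixed known probabilities, putting such ratings in the control part leaves the average effect being estimated unchanged. It does not bias the effect even if the mood model is wrong. At stake is the width of the confidence intervals for effects assumed to be as small as 0.1 standard deviations, in the analysis meant to show which types and timings of message work best.

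**Working it through.** **Inputs from the article.** Power and level: "We will perform sample size calculation at the usual 80% power at 5% level of significance" (two-sided assumed). Effect 0.1, constant over days; 60 daily randomisations; probabilities 0.5 and 1/3; stated sizes 55, 76 and 126. Losses: "Assuming each participant has an expected 70% response rate to the sent messages and 15% of the participants are expected drop off".

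**Assumptions.** The correlations of 0.2 and 0.4, given for change from baseline in the between-arm calculation, are applied to the raw rating as exchangeable. The effect of 0.1 is scaled by the total standard deviation.

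**Step 1: reproduce the plan's sizes without a mood covariate.** The noncentrality is N × 60 × b′Sb, where S is the covariance of the centred dummies. It is referred to a noncentral F with p and N − q − p degrees of freedom (q = 2 here; the required sizes do not change for q from 1 to 9).
- Message (p = 1): 60 × 0.25 × 0.1² = 0.15 per participant. At N = 55 the noncentrality is 8.25 and power is 80.5%; N = 54 gives 79.7%. The stated 55 is reproduced.
- Timing (p = 2, both effects 0.1): b′Sb = 0.01 × (2/9 + 2/9 − 2/9) = 0.00222, and × 60 = 0.1333 per participant. At N = 76 the noncentrality is 10.13 and power is 80.4%; N = 75 gives 79.8%. The stated 76 is reproduced.
- Inflation: 76 / 0.7 / 0.85 = 127.7, close to the stated 126.

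The plan's sizes therefore rest on the full, unadjusted error variance.

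**Step 2: variance removed by earlier mood.** With k earlier ratings, the R² of today's rating on their mean is kρ² / (1 + (k − 1)ρ). At k = 59 this is 2.36/12.6 = 0.19 for ρ = 0.2 and 9.44/24.2 = 0.39 for ρ = 0.4. Averaged over days 1 to 60:

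| | ρ = 0.2 | ρ = 0.4 |
|---|---|---|
| Full response | 0.161 | 0.359 |
| 70% response | 0.151 | 0.347 |

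Residual variance falls by about 15-16% or 35-36%. With full response, interval width scales by √0.839 = 0.92 or √0.641 = 0.80, so intervals are about 8% or 20% narrower.

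**Step 3: power with the noncentrality divided by (1 − R²).** The rows for 126 and 190 use 85% retention (107.1 and 161.5 participants) and 70% response.

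| Test, UR-arm N | Unadjusted | ρ = 0.2 | ρ = 0.4 | Gain (points) |
|---|---|---|---|---|
| Message, 55 | 80.5% | 86.8% | 94.1% | 6.3 to 13.6 |
| Timing, 76 | 80.4% | 87.1% | 94.6% | 6.7 to 14.3 |
| Timing, 126 | 80.3% | 86.7% | 94.2% | 6.3 to 13.9 |
| Message, 126 | 91.3% | 95.0% | 98.4% | 3.7 to 7.1 |
| Timing, 190 | 94.1% | 97.0% | 99.3% | 2.9 to 5.2 |
| Message, 190 | 98.4% | 99.4% | 99.9% | 1.0 to 1.5 |

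At the design sizes, ρ = 0.1 gives a gain of about 3 points and ρ = 0.5 about 17. The size needed for 80% power falls from 55 to 46 or 36 (message) and from 76 to 64 or 50 (timing). A single previous-day rating in place of the running mean recovers only about 1.5 points (ρ = 0.2) to 6 or 7 points (ρ = 0.4).

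**Step 4: simulation.** WCLS with cluster-robust errors for the message test at N = 55 (1,500 replicates) gave 80.8% rising to 86.5% at ρ = 0.2, and 80.4% rising to 94.3% at ρ = 0.4. In a separate simulation the mean estimates stayed near 0.10 with and without the covariate. Type I error there was 0.043 unadjusted and 0.033 adjusted.

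**The case against.** **Nothing falls short of plan.** The sizes of 55 and 76 reproduce without the covariate, so the analysis described is the analysis that was sized. This stands. A reader might infer that the trial loses 6 to 14 points of power, or that the estimate is biased. The article supports neither: planned power is met and the centred estimate is valid.

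**The gain depends on the arm size.** The article also states 190 per group for the mood comparison and keeps recruitment open at least to April 2021 or while funding lasts. At 190 the gain is about 1 to 5 points. This stands too, although the stated minimum is 128 participants in total, so a smaller UR arm is possible.

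**The correlations are borrowed.** They describe change from baseline in a different analysis, and no correlation for the raw rating is given. This stands, and every figure here is conditional on it.

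**Covariates are often left to a fuller analysis plan, and the list is introduced as what the covariates include.** This carries little weight. The section fixes the model down to dummy coding and centring, and it names weekday but no earlier mood. The point is a better choice within a stated model, not a request for missing detail.

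**The binary analysis.** All calculations are for the continuous model, so no gain has been shown for the dichotomised outcome.

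**Conclusion.** The point holds as one of efficiency in a secondary analysis. The UR-arm model as specified is valid and reaches its planned 80% power, but it leaves between-person mood variance in the error when data to remove much of it are already collected.

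The size is conditional on exchangeable correlations of 0.2 to 0.4 for the raw rating, a constant effect of 0.1 total standard deviations, and use of the running mean. On those terms intervals narrow by about 8-20%. The power gain ranges from 6-14 points at the design sizes, and for timing at 126, down to about 1-5 points at 190 per group. A weaker correlation, or recruitment beyond the target, shrinks the power gain further. The change is still worth making because it does not alter the estimand and costs almost nothing.

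**What to change.** In the Secondary Analysis section, add to the WCLS control covariates, and not to the effect-moderator part, the running mean of the participant's available mood ratings from days before the current day. Add an indicator for days with no earlier rating, with the mean set to a fixed value such as the sample mean on those days. Use only ratings that precede that day's randomisation. Keep the centring at 0.5 and 0.33, working independence and the robust variance, and report the unadjusted model as a sensitivity analysis. The same covariate may be used in the binary WCLS analysis, with a note that its benefit there has not been quantified.

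The cost is one sentence in the plan, a few lines of code and two extra parameters. No new data or participants are needed. Fixing the covariate in advance also avoids a later data-driven choice.
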